### Eligibility criteria

Children are eligible for the trial if they meet the following inclusion criteria:Age between 9 and 15 years old (confirmed from the date of birth recorded on the school registers)Enrolled in a participating primary school in the Mwea sub-county, Kirinyaga CountyConfirmed *S. mansoni* infection (confirmed by eggs in stool)A resident of Mwea sub-county, Kirinyaga County, central KenyaAble to take oral treatmentSigned informed consent by parent/guardian and oral assent from the child

Children who meet any of the following criteria will be excluded from participation in the study:Bodyweight ≥ 50 kgHemoglobin level ≤ 8.0 g/dLCo-infection with *Plasmodium falciparum* infectionSigns of severe malnutrition (evidenced by severe wasting [defined as weight-for-height < − 3SD] or mid-upper arm circumference [MUAC] < 12 cm)Current or history of convulsionsHistory of hypersensitivity to artesunates, sulfonamides, amodiaquine, mefloquine, or praziquantelHistory of treatment using an anti-malaria or anti-schistosomal drug within 28 days before enrollment in the study

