The artemisinin derivatives (artesunate, artemether, and dihydroartemisinin) are promising candidates for the treatment and chemoprophylaxis of schistosomiasis [18, 19]. This class of drugs is currently the most potent for treating malaria, for which they are used as artemisinin-based combination therapy (ACT) [20]. Artemisinin derivatives are specifically effective against the juvenile worms of the parasite [17, 19]. These differences in the mechanism of drug action support a theoretical basis for combining praziquantel with an ACT in treating schistosomiasis. The combination is likely synergistic, acting at two stages of the schistosome life cycle to cure the primary infection and block further transmission, especially in high-transmission areas. Data on the efficacy and safety of ACTs in treating schistosomiasis are scarce. However, compared to praziquantel, ACTs demonstrated significantly lower cure rates in treating children with schistosomiasis [21–24]. The results of the two studies that compared the efficacy of praziquantel plus dihydroartemisinin-piperaquine or praziquantel plus artesunate-mefloquine to praziquantel alone in the treatment of children with schistosomiasis were inconsistent [25, 26]. In one small study, praziquantel plus artesunate-mefloquine showed no benefit in the treatment of *S. haematobium*, while in a large trial, praziquantel plus dihydroartemisinin-piperaquine was associated with a substantial benefit in the treatment of *S. mansoni* [25, 26]. Hence, the additional benefit of adding an ACT to the standard praziquantel treatment for schistosomiasis remains unclear.

There is no systematic data from a single study comparing the efficacy of praziquantel plus an ACT to praziquantel alone on schistosomiasis. However, a systematic review of the available scanty evidence concluded that combining an artemisinin derivative plus praziquantel was more effective than praziquantel monotherapy [27]. WHO has approved at least five ACTs for the treatment of uncomplicated malaria: artemether-lumefantrine, artesunate plus amodiaquine, artesunate plus sulfadoxine-pyrimethamine, artesunate plus mefloquine, and dihydroartemisinin-piperaquine [20]. It is unclear which ACTs are effective and safe for treating schistosomiasis when combined with praziquantel.

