### Study area and population

This study population comprises primary school-age children (9–15 years) from selected primary schools in the Mwea East and Mwea West sub-counties in Kirinyaga County, central Kenya. The schools are eligible for inclusion if they have at least 50 pupils infected with *S. mansoni* detected from a screening exercise*.* The area is endemic for *S. mansoni*, with up to 75% prevalence in school children [28]. The major socio-economic activities in the study area are rice growing under irrigation and small-scale subsistence farming. Malaria transmission in the area is extremely low (< 1/1000 individuals), and elimination is envisaged.

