### Randomization and blinding

The randomization (in blocks of 15) list was computer-generated by an independent statistician not involved in participant management. The resulting sequence (randomization number and treatment arm) is stored in opaque sealed envelopes. The enrolling clinician assigns a study number to the participant. The study nurse implements the treatment allocation by opening a sealed envelope for each child according to the assigned randomization number. The laboratory staff are blinded to the treatment allocation, but participants, clinical staff, and data analysts are not.

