### Study procedures

#### Screening, enrollment, and participant follow-up

Potential participants were approached through the primary school system. At screening, every child provides a fresh stool (about 5 g) sample, which is used to detect the presence of *S. mansoni*. The geohelminths (hookworms, *Ascaris lumbricoides*, and *Trichuris trichiura*) are recorded. A capillary blood sample is taken by fingerprick to estimate hemoglobin and determine the presence of malaria parasites. Every child who tests positive for *S. mansoni* is invited for confirmation of eligibility. Eligible children will be recruited until the sample size is attained. The benefits of treatment for schistosomiasis and the availability of free medical check-ups were explained to potential participants to encourage participation and to ensure that adequate numbers were enrolled. Ineligible children are treated using a single oral dose of PZQ and referred for further treatment if need be.

At enrollment, verbal assent from the child and written informed consent from the parent/guardian are obtained. The study clinician takes a standard baseline medical history and performs a clinical examination, including weight (using a digital weighing scale), height (using a stadiometer), and temperature (using a digital thermometer) measurements. The clinician also assesses the size of the liver and spleen. All this information will be recorded on a paper-based case record form, which the principal investigator reviews to ensure compliance with the study protocol. Children receive study treatment according to the randomization list. Administration of all the study drugs is directly observed by the study nurse. All study drugs are given orally by the study nurse. For each child, the nurse records whether they have received their scheduled treatment, the dose, and reasons for missing treatment. A copy of the treatment sheet with dosing regimens is provided as supplemental material (Additional file 1: Appendix 4).

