### Treatment

The participants are allocated individually to treatment groups. The treatments administered in this study are as follows:Praziquantel (PZQ) (Biltricide, Bayer Healthcare, Leverkusen, Germany) is a tablet with 600 mg active ingredient. PZQ is administered as a single oral dose of 40 mg/kg body weight.Artesunate plus sulfamethoxypyrazine/pyrimethamine (AS+SP) (Coarinate Junior, Dafra Pharma, Turnhout, Belgium) is a fixed-dose combination tablet consisting of 100 mg artesunate, 250 mg sulfamethoxypyrazine, and 12.5 mg pyrimethamine. Participants receive a dose of artesunate plus sulfalene/pyrimethamine (4 mg/kg of the artesunate component) tablets once daily for 3 days.Artesunate plus amodiaquine (AS+AQ) (ASAQ, Winthrop, Sanofi-Aventis, France) is a fixed-dose combination tablet consisting of 100 mg artesunate and 270 mg amodiaquine. Participants receive a dose of artesunate plus amodiaquine (4 mg/kg of the artesunate component) tablets once daily for 3 days.Artesunate plus mefloquine (AS+MQ) (ARTEQUIN, Acino/Mepha, Switzerland) is a fixed-dose combination tablet consisting of 200 mg artesunate and 250 mg mefloquine. Participants receive a dose of artesunate plus mefloquine (4 mg/kg of the artesunate and 8.3 mg/kg/day of mefloquine) tablets once daily for 3 days.Dihydroartemisinin-piperaquine (DHAP) (D-ARTEPP, Guilin Pharmaceutical Co. Ltd, China) is a fixed-dose combination tablet containing 40 mg of dihydroartemisinin and 320 mg of piperaquine. Participants receive a dose of dihydroartemisinin-piperaquine (4 mg/kg/day of dihydroartemisinin and 20 mg/kg/day of piperaquine) tablets once daily for 3 days.

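### The allergy exclusion leaves out piperaquine, the partner drug in one of the four ACT arms

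*Protocol article*

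**What the plan says.** The exclusion list under Eligibility criteria in the protocol article rules out a history of "hypersensitivity to artesunates, sulfonamides, amodiaquine, mefloquine, or" praziquantel. The next criterion rules out recent use of an "anti-malaria or anti-schistosomal drug within 28 days before enrollment in the study". No exclusion refers to study drugs in general.

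The Treatment section describes four ACTs, each given with praziquantel. The fourth, DHAP, "is a fixed-dose combination tablet containing 40 mg of dihydroartemisinin and 320 mg of piperaquine". The Introduction treats the artemisinin compounds as separate members of a class: "The artemisinin derivatives (artesunate, artemether, and dihydroartemisinin").

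On who might notice an allergy, the section on screening, enrollment and follow-up says: "The study clinician takes a standard baseline medical history", and "Administration of all the study drugs is directly observed by the study nurse". The Randomization and blinding section adds: "The laboratory staff are blinded to the treatment allocation, but participants, clinical staff, and data analysts are not".

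**The concern.** Each child is randomized once across all five arms, so a child must be fit for every arm before the envelope is opened. A criterion that lists allergies drug by drug has to cover every drug the child could be given. This one covers the partner drugs of three ACTs and omits that of the fourth.

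What is at stake is participant safety in one arm. A child known to react to piperaquine meets the entry criteria as published and can be allocated a three-day course of it. If staff then withhold the drug, they do so by individual judgement after randomization, and the Withdrawal section says withdrawn children are not replaced. The non-inferiority comparison, the error rate and the sample size are untouched.

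**Working it through.** The plan gives no figure to reproduce here. The check sets the drug contents in the Treatment section against the allergy list in the Eligibility criteria.

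**Step 1: components named, reading artesunates literally**

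| ACT | Components | On the list | Count |
|---|---|---|---|
| AS+SP | artesunate, sulfamethoxypyrazine, pyrimethamine | artesunate; sulfamethoxypyrazine through its class (sulfonamides) | 2 of 3 |
| AS+AQ | artesunate, amodiaquine | both | 2 of 2 |
| AS+MQ | artesunate, mefloquine | both | 2 of 2 |
| DHAP | dihydroartemisinin, piperaquine | neither | 0 of 2 |

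Pyrimethamine is also unnamed, but in this trial it is given only in the same tablet as a listed sulfonamide.

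**Step 2: artesunates read as the whole artemisinin class**

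DHAP rises to 1 of 2 and the other counts do not change. A reaction to the combined tablet would then exclude the child; a reaction attributed to piperaquine alone would not. The Introduction's separate listing of artesunate and dihydroartemisinin gives the literal reading some support but does not settle the matter.

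**Step 3: partner drugs**

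On either reading, the non-artemisinin partner or its class is named for 3 of 4 ACTs. Piperaquine is the one missing.

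**Step 4: does another stated rule close the gap?**

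- The antimalarial exclusion looks back only 28 days and concerns treatment, not reactions.
- The baseline medical history may reveal a reaction, but no criterion acts on it.
- The discontinuation criteria contain no allergy history; their serious-adverse-event item applies only after exposure.
- The list of contra-indicated medicines appears under Concomitant treatment.
- The one-hour observation after dosing (Adverse events) detects a reaction but does not prevent it.

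None of these excludes the child before randomization.

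**Step 5: chance of assignment**

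Allocation is 1:1:1:1:1, with 108 of 540 children per arm (Sample size). For an eligible child, the chance of assignment to DHAP is 108/540 = 0.20, or 20%. The chance of being dosed is lower, because clinical staff know the allocation and may withhold the drug. The article gives no prevalence of piperaquine reactions, so no expected count can be derived.

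**The case against.** The strongest reply is that a journal article condenses protocol version 1.2, which is not shown and may contain a wider criterion. That limits what can be said about the conduct of the trial: nothing shows that a child with such an allergy was treated as eligible. It does not remove the defect in the published wording. The article does not summarise the rule; it spells it out drug by drug, includes the partners of the other three ACTs, and drops one.

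A second reply concerns consistency. If pyrimethamine can be excused because it comes only in a tablet with a listed drug, piperaquine could be excused in the same way once artesunates is taken to mean the class. This has force. On that reading the gap narrows to reactions attributed to piperaquine itself, and a history of reacting to a two-drug tablet will seldom separate the components. The gap becomes smaller but does not close.

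Third, the practical consequence is slight. The article says "Malaria transmission in the area is extremely low" (below 1 per 1000), so earlier exposure should be rare. A clinician takes a history, the principal investigator reviews the case record form, a nurse observes each dose, and adverse events are reported by arm. All of this stands and is why the point is minor. The form review, however, checks compliance with the protocol, and this child would comply.

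Finally, recruitment has ended, and the article does not show that the standard history recorded piperaquine reactions, so a look back through the forms may find nothing. That is fair and limits the value of the check for this trial. It is no argument against correcting the wording, which may be reused.

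**Conclusion.** The concern holds as a minor participant-safety defect in the wording of one eligibility criterion. The published list names the partner drug or its class for three of the four ACTs and omits piperaquine, and no other stated rule excludes a child known to react to it. Such a child would be eligible, with a 20% chance of assignment to the DHAP arm and a lower chance of being dosed. Few if any children are likely to be affected, and no estimate or conclusion of the trial changes.

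This rests on two assumptions: that the published list is the complete criterion, and that prior piperaquine exposure is uncommon in this area. The first cannot be checked without the full protocol. The second is inferred from the malaria figure the article gives.

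**What to change.** Reword the criterion as: *history of hypersensitivity to praziquantel, any artemisinin derivative, sulfonamides, amodiaquine, mefloquine, piperaquine, or any other component of a study drug*, to be checked before the envelope is opened. This settles the meaning of artesunates and covers pyrimethamine as well.

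Recruitment closed on 30 November 2022, so new wording cannot protect children already dosed. For this trial, the sponsor should report the criterion actually applied at screening and check the baseline histories in the DHAP arm for a previous reaction to either component.

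The cost is one line of text and a review of one arm's case record forms (108 planned). Had the wording been in force at screening, at most a very few children would not have been enrolled. Neither the sample size nor the analysis changes.

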### Randomization and blinding

The randomization (in blocks of 15) list was computer-generated by an independent statistician not involved in participant management. The resulting sequence (randomization number and treatment arm) is stored in opaque sealed envelopes. The enrolling clinician assigns a study number to the participant. The study nurse implements the treatment allocation by opening a sealed envelope for each child according to the assigned randomization number. The laboratory staff are blinded to the treatment allocation, but participants, clinical staff, and data analysts are not.

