### Study design

The SCHISTOACT study is designed as a phase III, open-label, five-arm, head-to-head, proof-of-concept, individually randomized, controlled, non-inferiority trial. The participants are randomly allocated (ratio 1:1:1:1:1) individually to one of five treatment groups. At baseline, participants in the control arm receive praziquantel (PZQ, single dose of 40 mg/kg). Those in the intervention arms receive a single dose of praziquantel (40 mg/kg) plus a 3-day course of one of four artemisinin-based combination therapies (4 mg/kg of the artemisinin component, once a day for three consecutive days, as fixed-dose WHO-recommended combination treatment for uncomplicated falciparum malaria). The four artemisinin-based combination therapies (ACTs) that are combined with praziquantel are artesunate plus sulfalene/pyrimethamine, artesunate plus amodiaquine, artesunate plus mefloquine, and dihydroartemisinin-piperaquine. These four ACTs were selected because they are widely available for malaria treatment, co-formulated, for once-daily dosing therapy, have a well-established safety profile and have all been evaluated for treating schistosomiasis with inconclusive results. The 6-week interval between the administration of study treatment and evaluation of primary endpoints has been chosen because it corresponds to the duration of schistosome larval maturation. The participants will be followed up at 6 and 12 weeks. During these follow-up visits, stool samples will be collected, and clinical assessments will be performed. All children will receive a standard dose of praziquantel at the end of the study. The study flow chart is shown in Fig. 1.

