#### Consenting process

A meeting was held with parents, teachers, and community leaders to inform them about the study’s aims, procedures, potential benefits, and risks. Permission to conduct the study is obtained from the Kirinyaga County Commissioner, the Kirinyaga County Directorates of Health and Education, and the respective school administration. School children in grades 3 to 5, aged between 9 and 15 years old, are informed about the study and asked to provide a stool sample to be tested for *S. mansoni*. Children and parents/guardians of all children who test positive for *S. mansoni* are invited to a meeting where general information about schistosomiasis, the aims of the study, procedures, potential risks, and benefits are explained in the local languages (Swahili and Kikuyu) and in a culturally sensitive way. The study nurse obtains written informed consent from the parents/guardians and verbal assent from the child. All the study personnel are trained in GCP. We explain that no biological samples are stored for any ancillary studies. A copy of the child assent and parental informed consent used in the study is provided in an online supplemental file (Additional file 1: Appendices 1–3).

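### One fixed block size of 15 in an open-label trial leaves allocation concealment only partly protected

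*Protocol article*

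**What the plan says.** Under Study design the trial is "designed as a phase III, open-label, five-arm, head-to-head, proof-of-concept, individually randomized, controlled, non-inferiority trial", and "The participants are randomly allocated (ratio 1:1:1:1:1) individually to one of five treatment groups".

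Randomization and blinding sets out the allocation procedure. On how the list was made, it says: "The randomization (in blocks of 15) list was computer-generated by an independent statistician not involved in participant management". On how the list is kept from staff, it says: "The resulting sequence (randomization number and treatment arm) is stored in opaque sealed envelopes". The clinician's part comes next: "The enrolling clinician assigns a study number to the participant". The nurse's part follows: "The study nurse implements the treatment allocation by opening a sealed envelope for each child according to the assigned randomization number". The same section says that laboratory staff are blinded and that participants, clinical staff and data analysts are not.

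Two other sections add to the nurse's role. Under Consenting process, "The study nurse obtains written informed consent from the parents/guardians and verbal assent from the child". Under Screening, enrollment, and participant follow-up, "All study drugs are given orally by the study nurse".

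Table 1 puts stool examination and the eligibility screen five days before D0, and consent, randomization and the first dose on D0. Sample size gives 540 children, 108 per arm.

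**The concern.** With five arms in equal ratio, a block of 15 holds exactly three places per arm. In an open-label trial each allocation is visible once it is made. Anyone who knows the block size and counts can therefore see arms being used up and, at the end of a block, can name the next arm. Opaque envelopes hide what is inside them. They do not hide what the remaining places must be.

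This matters because the nurse role that opens the envelopes also takes consent, on the day of randomization, when the screening stool result is already available. Someone who can guess the next arm could influence when a child is entered, or whether the child is entered at all. The result would be selection bias in the comparison of each combination with praziquantel alone, for both the week 6 cure rate and adverse events. Blinded slide reading protects how the outcome is measured. It does not protect who enters which arm.

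**Working it through.** The article gives no predictability figure, so there is nothing of its own to reproduce. The figures below use only its design inputs.

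**Inputs**
- Block size 15, the only one given (Randomization and blinding).
- Five arms, 1:1:1:1:1 (Study design), so 15/5 = 3 places per arm per block.
- 540 children (Sample size), so 540/15 = 36 complete blocks.
- Assumption: the observer knows the block size and where blocks begin, and tallies every allocation. The article does not say this is so, which makes the results upper bounds.

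**1. Allocations known with certainty.** The next arm is certain when all remaining places in the block belong to one arm.
- Last place: probability 1.
- Last two places in the same arm: 2/14 = 1/7.
- Last three places in the same arm: (2/14) × (1/13) = 1/91.
- Expected number per block: 1 + 1/7 + 1/91 = 15/13 = 1.154.
- Share: 1.154/15 = 7.7%. Over 36 blocks: 41.5, about 42 of 540.

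**2. Praziquantel alone versus combination known with certainty.** This is the contrast behind every primary efficacy comparison.
- Combination certain (all three praziquantel-alone places used): the 12 combination places fall at random into the 4 gaps around the 3 praziquantel-alone places, so on average 12/4 = 3 come after the last of these.
- Praziquantel alone certain (all 12 combination places used): by the same argument, 3/13 = 0.231.
- Total: 3.231/15 = 21.5%. Over 36 blocks: about 116 of 540.

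**3. Best guess.** The observer always names the arm with most places left. Exact recursion over the remaining counts gives 5.68 correct guesses per block, so 5.68/15 = 37.9%, against 20% by chance. The rate rises from 20% at position 1 to 57% at position 14 and 100% at position 15. Even so, about 62% of best guesses are wrong overall.

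**4. Effect of other block sizes.** For a single known size, the best-guess rate is 45.7% with blocks of 5, 40.7% with 10, 37.9% with 15 and 36.0% with 20. For random mixtures, a simulated observer knew the set of possible sizes but not the size of the current block:

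| Scheme | Arm certain | Praziquantel alone vs combination certain | Best guess correct |
|---|---|---|---|
| Fixed 15 | 7.7% | 21.5% | 38% |
| Random 5/10/15 | about 3% | about 9% | about 40% |
| Random 10/15/20 | about 2% | about 6 to 7% | about 38% |

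Mixing larger sizes removes most of the certainty but barely changes the average guess. Including blocks of 5 makes guessing easier.

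**The case against.** The strongest reply is that the article describes a recognised method of concealment: a list made by someone outside participant management, opaque sealed envelopes, and separate roles for assigning the number and opening the envelope. This stands. A reader might infer that allocation is not concealed at all, but the text contradicts that.

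Second, prediction requires knowledge of the block size, and nothing says site staff had it. The article appeared on 27 November 2023, almost a year after recruitment closed, so printing the size there does not show that they did. This also stands, and it is why the figures are upper bounds.

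Third, a reader might infer that envelopes were used out of order or opened before consent, because the article does not state the order, the custody or how the study number relates to the randomization number. A condensed article may leave such detail to the full protocol, so no defect follows from its absence. Likewise, the study nurse is a role. The text does not show that one individual did everything.

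Fourth, there are mitigations. Eligibility rests largely on measured criteria, every positive child is invited, cure is read by blinded staff, and Data management and analysis provides for adjustment where baseline imbalance is suspected. These narrow the room for steering and allow adjustment for measured traits such as weight and egg count. They leave discretion over timing and consent, and they cannot adjust for traits that were not recorded.

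What the reply does not remove is that one fixed block size, visible allocations and a consent-taking role that opens envelopes are stated features of the design.

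**Conclusion.** The point holds as a limited weakness: concealment is present but only partly protected. On the assumption that staff knew or inferred the block size and kept a full tally, at most 7.7% of allocations (about 42 of 540) were certain. Praziquantel alone versus combination was certain for about 21.5%, and the best guess was right about 38% of the time against 20% by chance. If staff did not know the size or could not follow the sequence, the figures are lower.

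No bias is shown to have occurred, and its direction and size cannot be derived. A reader might argue that heavier infection lowers the chance of cure, so that steering would shift the result in a known direction. The article does not state that relationship, and this point does not rest on it.

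**What to change.** **For the plan.** Replace the single block size with randomly varied larger multiples of five, for example 10, 15 and 20, and state that the sizes are not disclosed to site staff. This lowers fully determined allocations from 7.7% to about 2%, and known praziquantel-alone versus combination status from 21.5% to about 6 to 7%. It leaves the average guess rate about where it is. Avoid blocks of 5. The cost is a different setting when the list is generated and slightly less exact arm totals.

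**For this trial.** Recruitment closed on 30 November 2022, so the list cannot be changed. Existing records still allow three steps:
- Compare baseline egg count and weight between end-of-block and other positions, within arms.
- Add a sensitivity analysis of the week 6 cure-rate difference that leaves out allocations that could be fully determined from the list (about 42 expected).
- Report the fixed block size, in an open-label trial, as a limitation.

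These need only the list, the enrolment order and the baseline data. With about 42 allocations across five arms (roughly 8 per arm), the checks can reveal gross steering but cannot rule out a subtler effect. Leaving out the fully determined allocations does not remove partial predictability elsewhere in the block.
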